## Introduction

National sentinel surveillance data showed a rapid increase in newly reported HIV cases among young students in China from 2010 to 2019. The HIV prevalence among student men who have sex with men (MSM) in China is substantially higher than that in the general student population, with regional comparisons revealing the highest prevalence in the southwest region [1].

As the economic and cultural center of southwest China [2], Chengdu was estimated to have up to 120,000 active MSM in 2018 [3]. In 2021, the estimated number of college MSM registered on social networking platforms in Chengdu reached 8401, accounting for 2.08% of the total male university student population [4]. Although students were not traditionally considered a high-risk population for HIV infection, surveillance data indicate a rapidly increasing proportion of students infected with HIV/AIDS in the 15- to 24-year age group nationwide [5]. Systematic reviews have reported HIV prevalence rates of 3.8% [6] to 4.4% [5] among university student MSM. Risky sexual behaviors are common [7]; moreover, 85% of student MSM in Chengdu reported meeting sexual partners through mobile social networking platforms [4].

To date, research on university student MSM in China has primarily relied on cross-sectional surveys [6], limiting the understanding of factors driving HIV transmission in this population. While intervention trials targeting MSM populations have been conducted, few have specifically focused on student MSM. The HIV prevalence among university student MSM highlights an urgent need for effective, evidence-based public health strategies tailored to this group [5]. Compared to other high-risk populations, prevention efforts targeting university student MSM in China remain insufficient and under-researched [8].

There is growing evidence that online interventions can effectively reduce HIV risk behaviors and promote HIV testing among MSM populations [9,10]. These findings underscore the potential of digital strategies in reducing HIV or sexually transmitted infection (STI) disparities among student MSM. Given this, it is crucial to evaluate the effectiveness of internet-based intervention programs in this population.

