### Study Population

#### Inclusion Criteria

Participants will be eligible for inclusion if they meet all of the following criteria: (1) male, aged 18 years or older; (2) currently enrolled university student (including students pursuing technical diplomas or undergraduate degrees); (3) self-identified MSM, defined as having engaged in sexual behaviors with men, including mutual masturbation, oral sex, or anal intercourse; (4) confirmed HIV-negative status at baseline screening; and (5) willing and able to provide written informed consent to participate in the study.

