### HIV-HCV-HBsAg-Syphilis Testing

#### Overview

Participants will be required to complete self-testing for HIV, HCV, HBsAg, and syphilis at baseline, as well as during both follow-up surveys. Only individuals who test negative for HIV at baseline will be eligible for enrollment in the cohort. All participants are tested at each follow-up using a four-in-one rapid diagnostic kit that simultaneously detects HIV, syphilis, HCV, and HBV. Any reactive screening result triggers referral for confirmatory testing in certified laboratories. If a participant tests positive for any infection marker, they are immediately referred to a certified medical institution for confirmatory diagnosis and treatment, in accordance with national guidelines.

It should be specifically noted that we have also taken into account the issue of the serological window periods. To minimize potential misclassification, we have incorporated several measures including repeat testing for recent exposures and comprehensive risk documentation.

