### Study End Points

The study has three predefined endpoints:

HIV seroconversion: Participants with a reactive HIV test result will receive posttest counseling and referral to the local CDC for confirmatory laboratory testing. If HIV infection is laboratory-confirmed, the participant will be withdrawn from further study follow-up and intervention activities.Loss to follow-up: Participants will be considered lost to follow-up if they fail to complete follow-up assessments and cannot be contacted despite repeated attempts.Study completion: Participants who complete the 12-month follow-up period and final HIV/STI testing will be considered as having completed the study.

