### Outcome Measures

#### Primary Outcome

HIV and syphilis incidence rate: The primary outcome is the change in HIV and syphilis incidence rates before and after the intervention, assessed by comparing the postintervention incidence with the baseline incidence among local student MSM populations.

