#### Secondary Outcomes

Secondary outcome measures include (1) changes in sexual behaviors (eg, condom use, number of sexual partners) before and after the intervention; (2) frequency of biomedical intervention utilization (eg, HIV testing, STI testing, PEP, PrEP use); and (3) changes in HIV and STI prevention knowledge and awareness levels.

Detailed definitions of outcome indicators, measurement methods, and data sources are summarized in Table 1.

**Table 1. T1:** Indicators of study outcomes.

Domain	Specific indicator	Definition	Data source
Primary outcomes			
HIV incidence	Comparison between intervention cohort and local student MSM attending university	New HIV cases confirmed by medical institutions per 100 person-years vs surveillance data (2025)	Laboratory reports at 12-month follow-up; CDC^b^ surveillance data
Syphilis incidence	Comparison between intervention cohort and local student MSM attending university	New syphilis cases confirmed by medical institutions per 100 person-years vs surveillance data (2025)	Laboratory reports at 12-month follow-up; CDC surveillance data
Secondary outcomes			
Behavioral Changes			
Risk behaviors	Condom use during anal intercourse Commercial sex engagement Multiple partners	% reporting “always use condoms” in past 3 months % reporting paid sex in past 3 months % with ≥2 sexual partners in past 3 months	Structured questionnaire
Substance use	Psychoactive substance use during sex	% reporting use of chemsex drugs in past 3 months	Structured questionnaire
Testing behaviors	HIV testing frequency STI^c^ screening	% tested for HIV in past 3 months % tested for STIs in past 3 months	Structured questionnaire
Biomedical uptake			
Prevention tools	Condom/lubricant use PrEP^d^/PEP^e^ utilization	% using condom/lubricant % PrEP/PEP initiations	Supply logs; pharmacy data
Attitudinal changes			
Prevention intention	Future condom use intent Testing willingness	% planning to use condoms % willing to undergo future HIV/STI tests	Structured questionnaire
Awareness changes			
Health literacy	PEP/PrEP knowledge HIV/STIs awareness	% correctly describing PEP/PrEP protocols % choosing the right core knowledge about HIV/STIs	Knowledge assessment

a MSM: men who have sex with men.

b CDC: Centers for Disease Control and Prevention.

c STI: sexually transmitted infection.

d PrEP: preexposure prophylaxis.

e PEP: postexposure prophylaxis.

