### Data Collection and Baseline Assessment: Ensuring Reliability of Self-Reported Data

The baseline survey collects sensitive data, including sexual behaviors, substance use, and HIV-related risk factors. Due to social desirability bias or privacy concerns, participants may underreport or misreport behaviors, potentially affecting data accuracy.

To address this, volunteers will emphasize the project’s strict confidentiality protocols when inviting participants to complete the questionnaire. Participants will be clearly informed that no PII is collected in the survey, all data are securely stored in the back-end system, and only the project manager has access to detailed records.

This study has limitations. The before-after self-controlled cohort design does not include a concurrent control group, which limits the ability to make causal inferences. However, a randomized controlled trial was not feasible due to ethical and operational considerations—specifically, the local ethics committee’s recommendation that all eligible university students should have access to the intervention resources. To mitigate this limitation, we will compare changes observed in this study with contemporaneous surveillance data from the Chengdu student MSM population, conduct sensitivity analyses to assess secular trends, and interpret outcomes cautiously in light of these contextual factors. Despite these constraints, the design remains appropriate for evaluating real-world implementation and effectiveness under routine public health conditions. While the assumed reduction in incidence may be optimistic, behavioral indicators such as HIV testing and PEP/PrEP uptake serve as sensitive early markers of intervention impact in this short-term cohort. Given the expected rarity of incident infections over 12 months in student MSM cohorts, we interpret incidence changes cautiously while relying on proximal behavioral outcomes with higher short-term sensitivity.

By proactively addressing these anticipated challenges through standardized training, robust recruitment and retention strategies, and comprehensive privacy protections, this study aims to ensure rigorous implementation while generating valuable insights into the feasibility and effectiveness of internet-based, peer-led HIV prevention interventions among university student MSM.

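### The syphilis primary outcome sets a cohort that is HIV-negative at entry against a surveillance population not restricted by HIV status

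*Protocol article*

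**What the plan says.** **Cohort side.** The Inclusion Criteria require "confirmed HIV-negative status at baseline screening", and the overview of the HIV-HCV-HBsAg-Syphilis Testing section repeats it: "Only individuals who test negative for HIV at baseline will be eligible for enrollment in the cohort". Under Study End Points, once HIV is laboratory-confirmed, "the participant will be withdrawn from further study follow-up and intervention activities". That also ends the man's observation for syphilis.

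**Comparator side.** Three places describe it:
- Primary Outcome: the result is assessed by "comparing the postintervention incidence with the baseline incidence among local student MSM populations".
- Table 1, syphilis row: "Comparison between intervention cohort and local student MSM attending university", defined as "New syphilis cases confirmed by medical institutions per 100 person-years vs surveillance data (2025".
- The limitations paragraph near the end of the Discussion: "we will compare changes observed in this study with contemporaneous surveillance data from the Chengdu student MSM population".

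None of the three mentions HIV status, and no standardisation by HIV status is described.

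**HIV prevalence.** The Introduction states: "Systematic reviews have reported HIV prevalence rates of 3.8% [6] to 4.4% [5] among university student MSM".

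**The concern.** A man already living with HIV can acquire syphilis and be counted in surveillance, but he cannot enter the cohort. If such men are in the surveillance data and have a higher syphilis rate than HIV-negative men, which is plausible because the two infections share a route of exposure, the comparator rate is raised for a reason unrelated to the intervention. Part of any apparent syphilis reduction would then come from who was compared.

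The HIV row of Table 1 is less exposed, because only HIV-negative men can become new HIV cases. The syphilis row has no such built-in protection.

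The comparison matters because syphilis incidence is a primary outcome and, as defined in Primary Outcome and Table 1, is judged against the external population. The limitations paragraph offers contemporaneous surveillance, sensitivity analyses for secular trend and cautious interpretation. The two analytic measures deal with time, not with the make-up of the comparator.

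**Working it through.** **The plan's own figure.** The Sample Size section gives 484, from HIV rates of 4 and 1 per 100 person-years, two-sided alpha 0.05, 80% power and 10% attrition. With one year per person, n = (1.960 + 0.842)² × (0.04 + 0.01) / (0.04 − 0.01)² = 7.849 × 0.05 / 0.0009 = 436.05. Dividing by 0.90 gives 484.5, so the figure reproduces. It concerns HIV only. The article gives no syphilis rate, effect size or power, so there is no planned syphilis figure to check.

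**Inputs for the mismatch.**
- p, the HIV-positive share of the comparator: 3.8% to 4.4% (Introduction), used as a stand-in because the make-up of the surveillance data is not given.
- k, the syphilis rate in HIV-positive men divided by that in HIV-negative men: not in the documents, so varied as an assumption.

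**Formula.** If HIV-negative men have rate s, the mixed comparator has rate s × (1 − p + pk) = s × [1 + p(k − 1)]. With no intervention effect the cohort has rate s, so the apparent relative reduction is 1 − 1/[1 + p(k − 1)].

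Example: p = 0.038 and k = 3 give 1 + 0.038 × 2 = 1.076, and 1 − 1/1.076 = 7.1%.

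| p | k = 1 | k = 2 | k = 3 | k = 5 | k = 8 |
|---|---|---|---|---|---|
| 2% (assumed) | 0 | 2.0% | 3.8% | 7.4% | 12.3% |
| 3.8% | 0 | 3.7% | 7.1% | 13.2% | 21.0% |
| 4.4% | 0 | 4.2% | 8.1% | 15.0% | 23.5% |
| 8% (assumed) | 0 | 7.4% | 13.8% | 24.2% | 35.9% |

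**Ratio needed for a larger distortion.** Solving for k gives k = 1 + [1/(1 − R) − 1]/p. A spurious reduction R of 25% needs k = 9.8 at p = 3.8%, or 8.6 at p = 4.4%. A 50% reduction needs 27.3 or 23.7.

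**Effect on a test.** Take 484 × 0.90 ≈ 436 person-years, a fixed reference rate, a normal approximation and an assumed HIV-negative syphilis rate of 2 to 8 per 100 person-years. The chance of a false significant reduction, nominally 2.5%, becomes about 3% to 4% at k = 2, 3.5% to 6.4% at k = 3 and 4.9% to 13.9% at k = 5.

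**Contribution of the withdrawal rule.** At 1 to 4 HIV infections per 100 person-years (Sample Size), the number found by month 6 is about 484 × 0.01 × 0.5 = 2.4 to 484 × 0.04 × 0.5 = 9.7 men. Each loses about half a year, which is 1.2 to 4.8 person-years, or at most about 1% of 436. A man found at month 12 loses nothing. The entry restriction, not withdrawal, accounts for almost all of the mismatch.

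**The case against.** The strongest case against the point has four parts.

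1. **The premise is inferred.** A reader might take the protocol to say that the surveillance population contains about 4% HIV-positive men. It does not. The 3.8% to 4.4% comes from systematic reviews, and Table 1 names only CDC surveillance data without saying whose person-time is counted. This stands, and is why the size above is conditional.

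2. **The net direction is not shown.** A reader might also infer that the comparison as a whole favours the intervention. The documents do not support that. Recruitment via Blued, expected to supply at least half the sample, gives priority to universities with historically higher HIV prevalence. All participants are actively tested for syphilis at both follow-ups, which raises detection. Syphilis at baseline is not an exclusion. Each could raise the cohort's rate. This stands too, but opposing biases of unknown size are no reason to keep one that can be removed.

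3. **The effect is small against sampling error.** At an assumed 4 per 100 person-years, 436 person-years give about 17.4 cases, a relative standard error of 1/√17.4 ≈ 24%. A shift of 4% to 15% lies within that. This is correct, and limits how much the point matters, but the shift is systematic and a longer follow-up or larger cohort would not remove it.

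4. **This is detail for a fuller document.** Extraction filters commonly are. Here, however, the article presents Table 1 as the detailed definition of the outcomes, and the population being compared is part of that definition. As written, the two sides do not match.

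It would also be too strong to call the cohort HIV-negative throughout. Seroconverters contribute time until confirmation, and the four-in-one kit reads HIV and syphilis together, so syphilis found at the visit of a first reactive HIV test is still observed.

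**Conclusion.** The point holds as a mismatch of definitions in a primary outcome: the cohort is HIV-negative at entry and followed only to confirmed HIV diagnosis, while the syphilis comparator has no stated HIV-status limit.

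The size rests on two assumptions: that HIV-positive men are in the surveillance data at roughly the review prevalence, and that their syphilis rate is higher. Under both, the component is modest, about 4% to 15% for rate ratios of 2 to 5. It vanishes at a ratio of 1 or if the surveillance data already exclude men known to have HIV. At the cited prevalence it cannot alone create a large apparent effect unless the ratio is extreme. It deserves correction because it is systematic, affects a primary outcome and can be removed by definition where HIV status is recorded.

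**What to change.** In Primary Outcome and the syphilis row of Table 1:

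- Define the comparator as student MSM not known to be HIV-positive at the start of their surveillance person-time, removing previously diagnosed men from both cases and denominator.
- End syphilis person-time at confirmed HIV diagnosis on both sides, so that syphilis found at the same visit as a first reactive HIV test counts on both sides.

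A filter on being HIV-negative at the time of the syphilis test would not achieve this. It would drop men newly positive for both infections from the comparator while the cohort still counted them.

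The documents do not show that the surveillance extract holds linked HIV status, so this must be checked first. If it does not, report the comparison with a sensitivity analysis that divides the comparator rate by 1 + p(k − 1) over a stated range of p and k, and limit the conclusion accordingly.

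**Cost:** a revised definition and, where HIV status is recorded, a restriction on the extract. Records with unknown HIV status would be lost or handled only by the sensitivity analysis. Recruitment, visits and testing are unchanged.

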### Statistical Analysis

Upon completion of data collection, all survey data will be exported from the Wenjuanxing platform for data cleaning and preprocessing to ensure accuracy, completeness, and consistency. Data management and analysis will be conducted using established statistical software packages, including SPSS, Stata, or R.

Descriptive statistics will be used to summarize participant characteristics and key study variables. Categorical variables will be presented as frequencies and percentages, while continuous variables will be reported as means with SD or medians with IQR, depending on data distribution. The normality of continuous variables will be assessed using Shapiro-Wilk tests and visual inspection of histograms/Q–Q plots. Univariate analyses, such as chi-square tests for categorical variables and *t* tests or nonparametric tests for continuous variables, will be used to assess preliminary associations between independent variables and outcome measures. Multivariate analysis will be performed using logistic regression models (for binary outcomes) to identify factors independently associated with key study end points, adjusting for potential confounders. If advanced statistical modeling (eg, Cox proportional hazards models, generalized estimating equations) is deemed necessary to address specific research questions or to handle longitudinal data, additional statistical expertise will be sought to ensure appropriate application and interpretation of these methods. A 2-sided *P* value <.05 will be considered statistically significant.

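### Change in the number of sexual partners is a named secondary outcome, but Table 1 defines it only as the share with 2 or more partners, so any change that stays at or above 2 is invisible

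*Protocol article*

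**What the plan says.** Under Secondary Outcomes, the protocol article lists first "changes in sexual behaviors (eg, condom use, number of sexual partners) before and after the intervention". It then states: "Detailed definitions of outcome indicators, measurement methods, and data sources are summarized in Table 1". In that table, the risk-behavior row has a single partner indicator, labelled as multiple partners and defined as the percentage "with ≥2 sexual partners in past 3 months". No mean, median, rate or banded distribution of partners is defined, and no reason is given for cutting at 2.

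The Statistical Analysis section offers "chi-square tests for categorical variables and *t* tests or nonparametric tests for continuous variables" and logistic regression for binary outcomes. It does not say which of these applies to partner number. Study Design describes a before-after cohort in which each participant is his own control.

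The limitations text, at the end of the section on the reliability of self-reported data, says of the rarity of infections: "we interpret incidence changes cautiously while relying on proximal behavioral outcomes with higher short-term sensitivity".

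**The concern.** The outcome as named is a count; the outcome as defined is a two-level version of it. Only a crossing between 0-1 and 2 or more registers. A large reduction that ends at 2 or above, or a large increase that starts there, is recorded as no change.

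The design is meant to measure change within each man, and the limitations text justifies leaning on behavioral outcomes by their short-term sensitivity. A cut at 2 can work against both aims for this outcome. The study could report no effect on partner number when numbers had fallen, or miss a rise among men with many partners. A count analysis added after the data are seen would be open to the charge of being post hoc, because Table 1 defines no count indicator.

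**Working it through.** **1. What follows from the definition alone.** Let X be the number of partners in the past 3 months. The Table 1 indicator is 1 if X ≥ 2 and 0 otherwise.

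| Baseline → follow-up | Change in count | Change in indicator |
|---|---|---|
| 10 → 2 | −8 | 0 |
| 2 → 10 | +8 | 0 |
| 2 → 1 | −1 | −1 |

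No assumption is needed for this step.

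**2. Number of pairs.** The Sample Size section gives 4 and 1 per 100 person-years, two-sided α .05, 80% power and 10% attrition. A two-sample Poisson comparison gives (1.960 + 0.842)² × (0.04 + 0.01)/(0.04 − 0.01)² = 7.849 × 55.56 = 436.05 person-years, and 436.05/0.9 = 484.5. This agrees with the stated 484. Completers: 484 × 0.9 = 435.6, about 436 pairs. The calculation concerns HIV incidence; the article states no power for the partner outcome.

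**3. Assumptions for power.** The article gives no partner distribution, correlation or expected effect, so all of these are assumed: negative binomial counts with mean 1.5, 2 or 3; dispersion k of 0.5, 1 or 3; latent within-person correlation of 0.3 or 0.6. That is 18 settings for each size of fall and 90 in all. The tests, at two-sided .05, are McNemar on ≥2 and Wilcoxon signed-rank on the count.

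To show the scale: with k = 1, P(X ≥ 2) = [m/(1+m)]². At m = 2 this is (2/3)² = 44.4%. After a 20% fall, m = 1.6 and it is (1.6/2.6)² = 37.9%, a drop of 6.5 points.

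**4. Uniform proportional fall.** Simulated power over the 18 settings:

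| Fall | McNemar on ≥2 | Signed-rank on count | Loss in points: range (median) |
|---|---|---|---|
| 10% | 10-38% | 17-79% | 4-45 (16) |
| 15% | 21-75% | 33-99% | 10-41 (25) |
| 20% | 31-94% | 56-100% | 6-40 (23) |
| 25% | 54-99.5% | 79-100% | 0.5-30 (12) |
| 30% | 73-100% | 91-100% | 0-23 (4) |

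A second model with a different structure (Poisson counts with person-level and visit-level gamma variation) agrees in direction. At mean 2, a 20% fall gives 65% against 90% (a repeat gave about 62% and 88%), and a 15% fall gives 38% against 65%.

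**5. Other patterns of change.**
- *Only the excess above 2 partners falls, by 30-50%.* McNemar power stays near 5%, while the count test reaches about 20-100%: a loss of about 15-95 points.
- *Only men at exactly 2 change: 20% or 40% of them move to 1.* The order reverses and the ≥2 share is ahead by about 5-73 points. For example, at mean 2, k = 1, correlation 0.6 and 40% moving, power is 61% on the share and 10% on the count.

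**The case against.** Four points can fairly be made for the plan.

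- *The count is not excluded.* A reader might infer that partner number will be analysed only as a percentage. The article does not say so. Table 1 defines indicators rather than assigning tests, and Statistical Analysis provides for continuous variables. This stands, but the only partner indicator defined is binary, so those methods have no defined count to work on.
- *The conclusion does not hang on it.* A reader might infer from "relying on proximal behavioral outcomes with higher short-term sensitivity" that partner number carries the study's conclusion. The same paragraph gives its examples: "behavioral indicators such as HIV testing and PEP/PrEP uptake serve as sensitive early markers of intervention impact". Partner number is not among them, and the reliance is on behavioral outcomes as a group. This stands, and it limits the importance of the point.
- *The power loss is not a fixed quantity.* It depends on an unknown distribution and on where change occurs, and it can reverse. This stands. The use of McNemar is also a choice made here, since the article names no paired test. It favors the share: for a 20% fall, an unpaired chi-square has 24-86% power in the same settings, against 31-94% for McNemar.
- *The share has merits.* It means what its label says, matches the percentage format of the other behavioral rows, and is less exposed to a few extreme or misreported counts. This is a good reason to keep it, but not a reason to leave the named count undefined.

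**Conclusion.** The mismatch is real: a count is named, and only a ≥2 share is defined. The blindness to change at or above 2 follows from the definition and needs no assumption.

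Its cost does rest on assumptions. With about 436 pairs and a uniform fall of 15-20%, the share loses roughly 6-41 points of power against a paired count analysis; over falls of 10-30% the range is 0-45. The loss is larger if only men with many partners change, and becomes an advantage for the share if change is confined to 2 versus 1. A single unconditional figure for lost power would not be supported.

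This is a secondary outcome on which the study is not powered. The change is worth making before follow-up data are analysed, but it does not threaten the primary comparison.

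**What to change.** In Table 1, define the partner outcome as the number of sexual partners in the past 3 months. Analyse it within person across baseline, month 6 and month 12, for example as a rate ratio from a log-link GEE with robust standard errors, with a Wilcoxon signed-rank test as a check against a heavy tail. If the questionnaire records partners in bands, analyse the ordered bands, for example with a proportional-odds GEE. Keep the ≥2 share as a reported indicator beside it, since it is the more sensitive measure when change lies between 2 partners and 1.

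The cost is a change of wording in Table 1 and the analysis text, with no extra participants or visits. A rate ratio is slightly less simple to report than a percentage and is sensitive to a few very high counts; the signed-rank check and the retained share cover this.

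The condition is that the questionnaires (Multimedia Appendices 3 and 4, not shown) record more than a yes/no item. If they do not, the fix cannot be made by wording alone: the follow-up questionnaire is stated to be identical to the baseline one, and 127 men had already completed baseline by the end of April 2025. In that case the outcome text should name the ≥2 share rather than the number of partners.

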### Study Setting

This study is scheduled to commence in June 2025 and conclude in June 2026. The research process will consist of the following sequential phases: participant recruitment, HIV/hepatitis C virus (HCV)/hepatitis B surface antigen (HBsAg)/syphilis testing, baseline survey, intervention implementation, midterm survey, and final follow-up survey.

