#### Recruitment via WeChat

Recruitment information will be disseminated through a dedicated WeChat official account (WeChat is a Chinese multipurpose messaging, social media, and mobile payment app developed by Tencent Inc), which will publish targeted enrollment announcements clearly specifying the study’s inclusion criteria. These announcements will also provide the WeChat contact information of designated student volunteers. Interested individuals will be instructed to contact these volunteers directly via WeChat, where the volunteers will conduct eligibility screening and coordinate preenrollment HIV and STI testing.

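### The Table 1 testing indicators do not exclude the tests the study itself requires, so as written they do not validly measure change in testing behaviour

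*Protocol article*

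**What the plan says.** Table 1, under Secondary Outcomes, gives two testing indicators, both taken from the structured questionnaire: the percentage "tested for HIV in past 3 months" and the percentage "tested for STIs in past 3 months". Neither carries an exclusion.

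The testing section (Overview) states: "Participants will be required to complete self-testing for HIV, HCV, HBsAg, and syphilis at baseline, as well as during both follow-up surveys". It adds that "Only individuals who test negative for HIV at baseline will be eligible for enrollment in the cohort". The kit covers HIV and syphilis together, so one study test satisfies both indicators.

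On order at baseline, Study Setting lists the phases as "testing, baseline survey, intervention implementation, midterm survey, and final follow-up survey", with the HIV, HCV, HBsAg and syphilis test heading that run. Recruitment via WeChat says "the volunteers will conduct eligibility screening and coordinate preenrollment HIV and STI testing". Survey Content and Follow-Up puts the baseline questionnaire at enrolment and says that the follow-up questionnaires have the same content.

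The limitations text in the Discussion expects incident infections to be rare and says that "behavioral indicators such as HIV testing and PEP/PrEP uptake serve as sensitive early markers of intervention impact".

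**The concern.** The indicator is meant to show whether participants test more often because of the intervention. A test that the study requires, tied to the same visit as the survey, meets the definition whatever the participant would have done unprompted. The value at each wave then depends on two things: own-initiative testing, which is of interest, and whether the study test falls inside the three-month recall window and is counted by the respondent, which is not.

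The design has no concurrent control group, so nothing inside the study would reveal the artefact. Testing is one of the behavioural outcomes that the authors intend to rely on because incidence will be sparse. A flat result could therefore be read as no effect, and a rise as success, when either could come from the test schedule.

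**Working it through.** **The plan's own figure.** The article gives no expected level, power or sample size for the testing indicators. Its one sample size, 484, rests on HIV incidence: (1.96 + 0.8416)² × (0.04 + 0.01) / (0.04 - 0.01)² = 436.05, and 436.05 / 0.9 = 484.5. It reproduces and is unaffected by this point.

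**Model.** Let p be the share with an own-initiative test in the past three months, and s the share whose study-required test falls in the window and is counted. Taking the two as independent:

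measured proportion = s + (1 - s)p

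With B for baseline and F for follow-up, the measured change is [s_F + (1 - s_F)p_F] - [s_B + (1 - s_B)p_B]. When s is the same at both waves, this reduces to (1 - s)(p_F - p_B).

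**Inputs.** The documents give no value for p. Two pairs are assumed, each a true gain of 20 points: 30% to 50%, and 50% to 70%.

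| Case | s_B, s_F | 30% to 50% measured as | 50% to 70% measured as |
|---|---|---|---|
| Study test counted at both waves | 1, 1 | 100% to 100% (0) | 100% to 100% (0) |
| Counted by 90% at both waves | 0.9, 0.9 | 93% to 95% (+2) | 95% to 97% (+2) |
| Counted at baseline; taken after the survey at follow-up | 1, 0 | 100% to 50% (-50) | 100% to 70% (-30) |
| Counted only at follow-up | 0, 1 | 30% to 100% (+70) | 50% to 100% (+50) |
| Study tests excluded at both waves | 0, 0 | 30% to 50% (+20) | 50% to 70% (+20) |

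Only the last row returns the true change. The fourth row gives the same gain with no change in behaviour: if p stays at 30%, the measured rise is 100 - 30 = 70 points.

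**Which case applies.** The sections quoted above put the entry test before the baseline survey, so s_B is at or near 1 on a literal reading. At follow-up, the Overview has test and survey together and Table 2 puts them in the same month; neither states an order. The literal reading therefore leads to the first or third row, depending on that unstated order. The fourth row needs respondents to leave out the entry test but count later ones.

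**Which study tests matter.** A repeat test follows a visit by 2 to 4 weeks. After month 0 or month 6 it therefore falls about five months before the next survey, outside the three-month window. The 6-month test is likewise outside the window at month 12. The distortion comes from the test tied to the same visit.

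**The case against.** The strongest reply is that Table 1 is a summary and the item wording sits in the questionnaires (Multimedia Appendices 3 and 4), which are not shown. If those items already ask only about tests outside the study, the indicator works. This stands as a limit on the claim. It does not remove it, because the article presents Table 1 as the detailed outcome definition and that definition has no exclusion.

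A reader might infer that the study test immediately precedes every survey and pins the indicator at 100% throughout. The documents support that order at baseline only. Even there the text is untidy: electronic consent opens the baseline questionnaire, the Abstract and Results name surveys before self-tests, and Table 2 ticks testing at months 6 and 12 but not at month 0, at odds with the required entry test. This makes the direction of bias uncertain; it does not validate the indicator.

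A reader might also infer that the scheduled repeat tests inflate the next wave. They mostly fall outside its window.

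Finally, it would be too strong to say that the study's conclusions rest on this indicator. The Discussion refers to a set of behavioural markers that includes PEP/PrEP uptake, and Table 1 also lists condom use, partner number, paid sex and chemsex. Study tests do not count towards any of these.

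**Conclusion.** The point holds as a fault in a stated definition. As Table 1 is written, the two testing indicators mix own-initiative testing with the study's own visit tests, and their before-after change is not a valid measure of testing behaviour. For an assumed true gain of 20 points, the measured change runs from -50 to +70 points across the cases shown, so the direction of bias is unknown.

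Those sizes rest on assumed values of p, on independence of p and s, and on all-or-none counting in the extreme cases. The false rise also needs respondents to treat an identical question differently at different waves, which is possible but not documented. The documents do not support saying that the indicator could never detect a change, because the unseen questionnaire items may already exclude study tests.

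This is one secondary domain and leaves the sample size untouched. It should still be corrected, because HIV testing is named among the markers used to interpret the study.

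**What to change.** Redefine both indicators in Table 1 as the percentage with at least one HIV (or STI) test in the past three months other than tests required by the study, namely the entry, 6-month, 12-month and scheduled repeat tests. Use identical wording at all waves. If the questionnaire items already say this, state it in Table 1 and no further change to the definition is needed. Report completion of study-required tests separately, as a feasibility measure. Say whether voluntary use of the STI self-test kit in the one-time prevention package counts. Reconcile Table 2 with the required baseline test.

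The cost is one questionnaire stem and one definition, but baselines already collected need care: 127 participants had completed theirs by the end of April 2025. They may need a short supplementary item asking about tests outside the study. Platform records could help only if they can be linked to survey answers. Kits carry unique numbers, but the article does not say that these separate study kits from own-initiative ones, nor does it describe linkage to the survey. A change of stem also departs from the rule that questionnaire content is identical across waves, so it should be documented. Participants whose baseline answer cannot be separated should be left out of the before-after comparison of this indicator, and their number reported.
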